### Phase 2: ASSIST-ICU Pragmatic Trial Design

The ASSIST-ICU pragmatic trial will use a prospective, nonrandomized, 2-unit pretest-posttest design. The specific components of the ASSIST-ICU CDSS and how the implementation will be operationalized, implemented, measured, and monitored for feasibility will be incorporated into the research protocol at the end of phase 1.

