#### Study Setting and Participants for Pragmatic Trial

This study will take place at University of Iowa Health Care. Within University of Iowa Health Care, we will include 2 adult ICUs. Both units have implemented comprehensive patient physical activity programs that include protocol-based activity progression, routine PT consultation on ICU admission, and standardized activity assessment and intervention documentation for RNs and PTs in the EHR. The ASSIST-ICU CDSS will include 2 participant groups: clinicians and patients. The clinicians will include all RNs and PTs working in the selected adult ICU units. RN-to-patient ratios in the ICUs are typically 1:2, and PTs usually manage 6 to 8 patients per day. Patients will include all adults admitted to a participating ICU for at least 24 hours. As a pragmatic trial focused on decision-making at the point of care, we will not place restrictions on age, comorbidities, severity of illness, or expected discharge outcomes.

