#### Intervention

As the trial involves using a prospective, nonrandomized, 2-unit pretest-posttest design, the ASSIST-ICU CDSS will be implemented in each ICU for a period of 9 months using a staggered approach, with 1 ICU receiving the intervention at a time. A training period will be conducted with RN and PT end users before implementation to facilitate effective use of the ASSIST-ICU CDSS and integration into existing workflows. Training will be scheduled based on each clinician’s schedule and last approximately 15 minutes. In addition, resource materials will be distributed to each unit before and throughout the trial.

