#### Data Collection and Analysis for Pragmatic Trial

Feasibility and effectiveness data will be captured via the EHR. Study data will be extracted from the EHR using EHR reports that are built from the structured data fields used to create the ASSIST-ICU CDSS. Baseline data will be collected via the reports before the intervention implementation using silent data collection. Silent data collection functionality allows CDSS logic to actively run in the system, but users do not yet have access to use the CDSS dashboard, allowing for baseline data collection.

We will evaluate key implementation and clinical outcomes by using the RE-AIM (reach, effectiveness, adoption, implementation, and maintenance) framework because it considers both the feasibility (reach, adoption, and implementation) and clinical effectiveness outcomes of the intervention (Table 3) [60].

The primary feasibility outcome will be physical activity decision-making (defined as the number of patients with out-of-bed activity documented and a corresponding CDSS designation of “safe” on a given ICU day). Secondary measures include acceptability and usability of CDSS. Acceptability (defined as the belief that an intervention is agreeable, palatable, or satisfactory [56]) and usability (defined as being appropriate for a specific context of use [55]) will be measured through online surveys. We will also evaluate potential safety events routinely reported in physical activity studies [61] and documented in the health system’s patient safety reporting system, including whether the following events occurred during out-of-bed activity: fall to the floor, unplanned extubation, or line removal requiring urgent replacement.

On trial completion, all ICU RNs and PTs who worked in a study ICU will be invited to participate in a web-based survey. Usability (SUS), cognitive workload (NASA-TLX), and acceptability (AIM) will be measured and calculated in the same manner as described for the simulated trial.

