We will generate histograms and bar charts to evaluate the distributions of all variables of interest and report appropriate descriptive statistics. Continuous variables will be summarized by means and SDs or medians and IQRs, as appropriate. Categorical variables will be summarized as counts and percentages. Preexisting differences in the outcome variables at baseline will be assessed using 2-sample *t* tests, the Wilcoxon rank sum test, or the Fisher exact test. Frequencies and percentages will be calculated to determine the feasibility of participation measures. A 2-sample binomial test will be used to test the null hypothesis that decision accuracy with the support tool does not differ from accuracy without it. Unit-stratified means and SDs will be calculated for SUS, NASA-TLX, and AIM scores. *P* values will be reported, and statistical significance will be evaluated at α=.05.

**Table 3 table3:** Study outcomes by RE-AIM (reach, effectiveness, adoption, implementation, and maintenance) element.

Elements and end points		Data collection

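### Significance tests of outcomes at baseline, followed by an unadjusted binomial test, cannot separate a tool effect from a change in patient mix between periods

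*Protocol article*

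**What the plan says.** All references are to the protocol article.

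- **Design** (Phase 2: ASSIST-ICU Pragmatic Trial Design): the trial "will use a prospective, nonrandomized, 2-unit pretest-posttest design".
- **Roll-out** (Intervention): the tool is "implemented in each ICU for a period of 9 months using a staggered approach, with 1 ICU receiving the intervention at a time".
- **Patients** (Study Setting and Participants for Pragmatic Trial): adults with an ICU stay of at least 24 hours, and "we will not place restrictions on age, comorbidities, severity of illness, or expected discharge outcomes".
- **Meaning of baseline** (Data Collection and Analysis for Pragmatic Trial): "Baseline data will be collected via the reports before the intervention implementation using silent data collection".
- **Comparability check** (same section): "Preexisting differences in the outcome variables at baseline will be assessed using 2-sample" procedures (*t*, Wilcoxon rank sum or Fisher exact). The groups are not named.
- **Effect test** (same section): accuracy with and without the tool is compared by a 2-sample binomial test. No covariate, unit term or time term is mentioned. Stratification by unit is stated only for the survey scores.
- **Description** (same section): "We will generate histograms and bar charts to evaluate the distributions of all variables of interest and report appropriate descriptive statistics". This is not said to be by period, and no patient characteristic is named.

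**The concern.** The effect is a comparison of patients treated without the tool and patients treated with it, at different calendar times and without randomisation. For that comparison the main question is whether the two sets of patients are alike. The stated check does not address it. It looks at outcomes rather than patients, and at the baseline period alone rather than across periods.

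Patient mix is likely to matter for these endpoints. Under ASSIST-ICU Algorithm Development, readiness is scored from respiratory, cardiovascular, neurological and other status, and a single failing domain makes the patient not ready. The primary feasibility outcome requires both recorded out-of-bed activity and a safe designation. A less sick intake can therefore raise that outcome through the designation itself, even if clinicians behave exactly as before. Time to first out-of-bed activity is plausibly sensitive to severity as well.

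A P value is also a poor measure of comparability. It depends on the number of patients, and a non-significant result does not show that groups are similar. At stake is whether a difference in this trial can be credited to the tool when the later multisite trial is planned.

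**Working it through.** **The plan's own figures.** The article gives no figure for this comparison. Its only power figure, 99.2%, belongs to the simulated trial. It reproduces closely (99.5% by the pooled z test with 25 × 6 = 150 decisions per arm, 75% against 50%, two-sided 0.05), and this point does not depend on it.

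**Step 1: what the stated check can see.** Baseline is the time before implementation, so two samples at baseline most plausibly means ICU 1 against ICU 2. If the two ICUs have equal baseline outcomes, that test is significant about 5% of the time, whatever happens to the patients afterwards. It carries no information about a later change in mix. If before against after was meant instead, testing the outcome variables would test the effect itself, not comparability. Neither reading answers the question.

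**Step 2: how a mix shift enters the unadjusted comparison.** Take two patient strata, sicker and other, with outcome rates r₁ and r₂ that the tool does not change. Let the sicker share move from s₀ to s₁. Then

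spurious change = (s₀ − s₁) × (r₂ − r₁).

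All inputs below are assumptions; none is in the documents.

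| s₀ → s₁ | r₁, r₂ | Before | After | Spurious change |
|---|---|---|---|---|
| 50% → 40% | 30%, 60% | 0.5×0.3 + 0.5×0.6 = 45% | 0.4×0.3 + 0.6×0.6 = 48% | +3 points |
| 50% → 40% | 20%, 60% | 0.5×0.2 + 0.5×0.6 = 40% | 0.4×0.2 + 0.6×0.6 = 44% | +4 points |
| 50% → 40% | 60%, 30% | 0.5×0.6 + 0.5×0.3 = 45% | 0.4×0.6 + 0.6×0.3 = 42% | −3 points |
| no shift | any | – | – | 0 |

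The second row describes raw out-of-bed activity, which is not the tested outcome. The third row matters because the tested quantity is decision accuracy. If accuracy is scored as in the simulated trial, keeping an unready patient in bed counts as correct. Accuracy could then be higher among sicker patients, and the error would run against the tool. The direction is therefore open.

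**Step 3: effect on the test.** For the 45% to 48% case with no tool effect, the chance that the unadjusted test is significant in favour of the tool, against a nominal 2.5% in that direction, is:

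| Independent observations per period | 200 | 400 | 800 | 1500 |
|---|---|---|---|---|
| Chance of a significant result | 8.7% | 13.4% | 22.4% | 37.7% |

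The error rate grows with sample size, because the bias stays fixed while the standard error shrinks.

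**Step 4: a P value as yardstick.** Suppose the right variable were tested across the right periods, and the share with a given characteristic moved between 40% and 50%. The chance of a significant result is 29% with 100 patients per period, 52% with 200 and 81% with 400. The same imbalance passes or fails according to numbers alone.

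**Step 5: whether a unit difference matters.** Assume baseline rates of 45% in one ICU and 55% in the other. With 400 per ICU the baseline test flags this with 81% power. A comparison within each unit is not biased by it. A pooled comparison can be: if the first ICU supplies 50% of the data without the tool and 40% of the data with it, the pooled rate moves from 0.5×45 + 0.5×55 = 50% to 0.4×45 + 0.6×55 = 51% with no tool effect.

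**The case against.** **A reader might infer that the plan tests the wrong contrast.** The documents do not support that. The groups are unnamed, so the comparison of ICUs is an inference. A baseline difference between ICUs is also relevant here: the roll-out is staggered, the stated test is not stratified by unit, and step 5 shows that pooling with unequal contributions lets a unit difference through. The same applies if the ICU not yet switched serves as a comparator. The check is insufficient, not irrelevant, and its descriptive content should stay.

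**A reader might infer that patient mix will go unexamined.** That goes too far. The article is a condensed account, descriptive statistics are planned for the variables of interest, unit-level barriers will be tracked (Study Limitations), and a full protocol or analysis plan may contain case-mix tables or adjustment. What stands is narrower: the article states a particular check and a particular unadjusted test, and the two together do not protect the comparison.

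**A reader might take 3 or 4 percentage points as the expected bias.** The inputs are assumed, the tested outcome is decision accuracy, and the sign can reverse.

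**The complaint about P values is partly a matter of preference.** In a nonrandomized study a test of preexisting difference is not meaningless, as it would be after randomisation. Nor does the article say that a non-significant result will be taken as comparability. That is fair, but a measure of imbalance that does not depend on sample size is still more useful.

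**This is a pilot with a feasibility outcome labelled primary.** That lowers the stakes. It does not remove them, because the article sets a hypothesis test of effectiveness at α=.05.

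**Conclusion.** The point holds in a limited form. The only comparability check stated for the pragmatic trial is significance testing of baseline outcomes between two unnamed groups, and the stated effect test is unadjusted. In a nonrandomized, staggered before-after design with no restriction on severity, this cannot show that patients in the two periods are comparable, so a change in mix may be read as a tool effect or may hide one.

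The documents do not establish the size. Across the assumed inputs above, the spurious change runs from −3 to +4 points, and it is zero if the mix does not move or the outcome does not depend on it. The error rates in step 3 also assume independent observations. The conclusion itself needs only two things: that patient mix can differ between periods, which open eligibility permits, and that the outcome varies with it, which the readiness rules make likely. It should be corrected before phase 2 starts; it does not invalidate the design.

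**What to change.** 1. Replace the sentence on baseline tests. Name the groups. Describe baseline outcomes by unit, and patient characteristics by unit and period, with standardised differences instead of P values.
2. Replace the unadjusted binomial test with a regression for the comparison of periods, for example logistic for a binary decision outcome. Include unit, calendar time and a short prespecified list of case-mix variables available in the EHR, such as age and ventilation status, plus severity if it can be extracted. With only two units, the time term has to be simple, because the tool can be separated from calendar time only in months when one ICU has it and the other does not.
3. Say openly that the model replaces the binomial test, and fix the covariate list before outcome data with the tool are examined.

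**Cost.** A model takes the place of a simple test, with more to specify and explain. The EHR reports are to be built from the fields used to create the tool; airway status is among those shown, but severity scores are not, so a few fields may have to be added. Phase 2 approval had not yet been sought when the article was written, so the change can go into that submission.

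### The ICU trial tests the tool's effect with a 2-sample binomial test, which does not fit a nonrandomised, staggered, two-unit pre-post design with an outcome counted by ICU day

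*Protocol article*

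**What the plan says.** The section Phase 2: ASSIST-ICU Pragmatic Trial Design sets the design: "The ASSIST-ICU pragmatic trial will use a prospective, nonrandomized, 2-unit pretest-posttest design". Under Intervention, the tool is to be "implemented in each ICU for a period of 9 months using a staggered approach, with 1 ICU receiving the intervention at a time". Under Study Setting and Participants, "Patients will include all adults admitted to a participating ICU for at least 24 hours", without restriction on severity or comorbidity.

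Data Collection and Analysis for Pragmatic Trial covers the data and the test:

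- Without-tool data: "Baseline data will be collected via the reports before the intervention implementation using silent data collection". Neither the length nor the calendar window of this baseline is given.
- Primary feasibility outcome: "the number of patients with out-of-bed activity documented and a corresponding CDSS designation of “safe” on a given ICU day". This is a count; no denominator is stated.
- Test of the tool's effect: "A 2-sample binomial test will be used to test the null hypothesis that decision accuracy with the support tool does not differ" (compared with no tool), at α=.05. The same sentence serves the simulated trial.
- Baseline: "Preexisting differences in the outcome variables at baseline will be assessed" by t, Wilcoxon or Fisher tests. No adjustment is said to follow.
- Unit: stratification is stated only for the survey scores (SUS, NASA-TLX, AIM).

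**The concern.** In the simulated trial, the control and intervention groups are concurrent, and the Discussion describes the efficacy test as randomised. A two-sample comparison is at least aligned with that design. The ICU trial has neither property, yet inherits the test.

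- **Independence.** A patient who stays several days can contribute several observations, and days from one patient resemble each other. A binomial variance is then too small.
- **Comparability over time.** In each unit the without-tool data precede the with-tool data. Seasonal, staffing or practice changes between the periods enter the estimate as tool effect. Study Limitations itself mentions turnover and temporary staffing as possibilities.
- **Comparability of units.** If one unit supplies a larger share of without-tool than of with-tool data, a difference between the units appears as a tool effect.

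Without randomisation, the analysis is the main protection against these errors. What is at stake is a significant result, of either sign, when the tool does nothing, in a study meant to justify a multisite trial.

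**Working it through.** **1. The plan's own figure.** The ICU trial has no stated sample size or power. The only power figure is 99.2% for the simulated trial (75% v 50% correct, 25 clinicians per group, 6 scenarios each). Treating this as 25 × 6 = 150 independent decisions per group gives 99.5% (z test) or 99.3% (continuity-corrected or Fisher), so the figure reproduces. One binary result per clinician (25 v 25) gives only 36% to 48%. A Wilcoxon test on the 0–6 scores gives 99.1%, so the figure alone does not prove which unit was analysed. It is consistent with counting each decision as independent.

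**2. Clustering.** Inputs, all assumed: *m* ICU days per patient and within-patient correlation ICC. Design effect DE = 1 + (*m* − 1) × ICC. The true size of a nominal 5% test is 2 × [1 − Φ(1.96/√DE)].

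| *m* | ICC | DE | True type I error |
|---|---|---|---|
| 3 | 0.1 | 1.2 | 7.4% |
| 4 | 0.2 | 1.6 | 12.1% |
| 5 | 0.3 | 2.2 | 18.6% |
| 5 | 0.5 | 3.0 | 25.8% |

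The size depends on the assumptions. The direction does not: any positive ICC with *m* > 1 gives DE > 1.

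**3. Calendar time.** Assume independent days and a rise from 50% to 55% that has nothing to do with the tool. With 2000 patient-days per period, the standard error is √(0.525 × 0.475 × 2/2000) = 0.0158 and z = 0.05/0.0158 = 3.17. The chance of significance is Φ(3.17 − 1.96) = 0.89. With 1000 days per period it is 0.61, and with 500 it is 0.35.

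**4. Unit mix.** With no tool effect, the spurious difference is (*w*with − *w*without) × (A2 − A1), where *w* is the second unit's share of each sample and A1, A2 are the unit accuracies. With equal baseline lengths and steady patient flow the shares are equal and the bias is zero. With assumed baselines of 9 and 18 months and 9 tool months each, it is (9/18 − 18/27) × 10 points = −1.7 points for a 10-point unit difference.

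**5. Together.** A simulation with no tool effect used those 9- and 18-month baselines over 27 months. It assumed 20 patients per unit-month, 50% accuracy, and geometric stays with a mean of 4 days, capped at 20. The first unit's time after its tool block was left out. There were 800 runs per row (Monte Carlo SE about 0.8 points near 5–7%, up to 1.8 near 50%). Entries are false-positive rates at nominal 5%.

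| Scenario | 2-sample test | Patient-clustered SE only | Unit and month terms, patient-clustered SE |
|---|---|---|---|
| ICC 0.1 | 11.4% | 4.5% | 5.9% |
| ICC 0.2 | 17.4% | 4.8% | 6.6% |
| ICC 0.3 | 25.6% | 4.6% | 5.8% |
| ICC 0.2, drift 2 points/year | 29.9% | 11.8% | 6.8% |
| ICC 0.2, drift 4 points/year | 54.0% | 28.4% | 6.1% |
| ICC 0.2, units differ by 10 points | 27.6% | 9.5% | 7.1% |
| ICC 0.2, drift 2 points/year, units differ by 10 points | 19.1% | 4.8% | 7.5% |

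Two checks:

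- The 17.4% exceeds the 12.1% of step 2 because stays vary. For a geometric stay with mean 4 (variance 12), the effective *m* is (12 + 16)/4 = 7, so DE = 2.2 and the formula gives 18.6%.
- In the last row the biases nearly cancel. With-tool data centre on month (13 + 22)/2 = 17.5 and without-tool data on (9 × 4 + 18 × 8.5)/27 = 7. Drift therefore adds 2 × 10.5/12 = 1.75 points, against −1.7 from the unit mix.

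Clustering alone does not remove bias from time or unit; all three terms are needed. The adjusted model simulated was linear, not logistic.

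**The case against.** The strongest reply is that the article condenses a fuller protocol and that an analysis plan may hold adjusted models. That does not answer the point, because the text names a test and does not merely omit detail. Patient, unit and time terms cannot be added to a 2-sample binomial test without replacing it. The design section defers the tool's components and how implementation is measured and monitored; it does not defer the test.

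Four further objections do stand and limit the claim.

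- **Pooling is inferred.** The article does not say that both units are merged into one unadjusted table. Separate pre-post comparisons in each unit would also fit the design label. They would remove the unit-mix problem but not clustering or calendar change.
- **Patient-days are inferred.** The outcome is a count without a denominator, and accuracy is not defined for the ICU trial. With one observation per patient, the inflation in step 2 disappears and the confounding by time remains.
- **A large unit bias is not shown.** A reader might construct, say, accuracies of 30% and 60% with baselines of 3 and 12 months, giving 45% with and 54% without the tool, a spurious −9 points. None of those inputs is in the document, and equal baselines give zero. What the document supports is that the baseline window is unstated.
- **A discarded concurrent control is not shown.** A reader might infer this from the phrase "using a staggered approach, with 1 ICU receiving the intervention at a time". The article does not say whether silent collection in the second ICU continues or stops while the first is live. The control is available; it is neither planned nor ruled out.

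Nor is this the only inferential test in the ICU trial, since baseline differences are tested too. It is the only test named for the tool's effect.

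**Conclusion.** The concern holds in this form: the article fixes a test for independent, comparable samples on a design that provides neither. If patient-days are analysed, with 3 to 5 days per patient and ICC 0.1 to 0.5, a nominal 5% test has a true size of about 7% to 26%. Calendar change is credited to the tool, in either direction. Unit differences bias the result only if the units' shares of baseline and tool time differ, which cannot be judged from the text.

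This should be fixed, but it is not fatal. The Abstract presents the work as a pilot for a later multisite trial, the tested measure appears to be the primary feasibility outcome, and no go/no-go rule is tied to the P value.

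**What to change.** 1. **Define the proportion.** For example: patient-days with documented out-of-bed activity among patient-days designated safe. If concordance in both directions is meant, as in Table 2 for the simulated trial, say so.
2. **Replace the test.** Use a logistic GEE or mixed model on patient-days, clustered on patient, with tool status, fixed unit and calendar-time terms, and admission-level case-mix from the EHR. Avoid daily status variables that mobilisation could itself change.
3. **Fix the baseline window.** State its dates. Start silent collection in both ICUs together and keep it running in the second while the first is live, so that the second is a concurrent control in that block.
4. **Do not use the first ICU as an unexposed control after its own block.** Its staff will have been trained and exposed for 9 months, and the maintenance row of Table 3 is about practice continuing after the trial. Code that time separately or exclude it.
5. **Report** the effect with its confidence interval, and state that inference is limited to these two units and assumes a common time trend.

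**Cost.** Analysis wording, plus leaving existing silent logic switched on. The phase 2 ethics application is still to be submitted, so timing is favourable. Confidence intervals will be wider. With a free effect for every month and item 4 applied, the tool effect is identified only from the shared baseline and the first block; the second ICU's tool block adds information only if time is modelled more smoothly, so that choice should be prespecified. Two units do not allow between-unit variance to be estimated, and clustering on patient does not cover correlation within nurse or therapist; both belong in the stated limitations.
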